## Abstract

**Background:**

Diagnostic capacity and suboptimal logistics are consistently identified as barriers to timely diagnosis of cancer, especially lung cancer. Immediate chest X-ray (CXR) reporting for patients referred from general practice is advocated in the National Optimal Lung Cancer Pathway to improve time to diagnosis of lung cancer and to reduce inappropriate urgent respiratory medicine referral for suspected cancer (2WW) referrals. The aim of radioX is to examine the impact of immediate reporting by radiographers of CXRs requested by general practice (GP) on lung cancer patient pathways.

**Methods:**

A two-way comparative study that will compare the time to diagnosis of lung cancer for patients. Internal comparison will be made between those who receive an immediate radiographer report of a GP CXR compared to standard radiographer GP CXR reporting over a 12-month period. External comparison will be made with a similar, neighbouring hospital trust that does not have radiographer CXR reporting. Primary outcome is the effect on the speed of the lung cancer pathway (diagnosis of cancer or discharge). Secondary outcomes include the effect of the pathway on efficiency including the number of repeat CXRs performed in a timely fashion for suspected infection and the effect of immediate reporting of GP CXRs on patient satisfaction.

**Discussion:**

The radioX trial will examine the hypothesis that immediate reporting of CXRs referred from GP reduces the time to diagnosis of lung cancer or discharge from the lung cancer pathway.

**Trial registration:**

International Standard Randomised Controlled Trial Number ISRCTN21818068. Registered on 20 June 2017.

**Electronic supplementary material:**

The online version of this article (doi:10.1186/s13063-017-2268-x) contains supplementary material, which is available to authorized users.

## Background

Lung cancer is the leading cause of cancer death worldwide [1]. When compared to other common cancers, the prognosis for lung cancer is worse [2]. In the United Kingdom (UK) there has been a recent modest increase in survival, with 12.6% of patients with lung cancer surviving for 5 years [3], although 30% of patients die within 90 days of diagnosis [4]. Diagnosis of lung cancer is often made at a late stage, when prognosis is poor [5], and several factors are thought to influence this. Symptoms suggesting lung cancer are often non-specific until late in the disease, which results in diagnostic difficulties in primary care [4, 6, 7]. In an attempt to address this, recent guidance by the National Institute for Health and Care Excellence (NICE) has lowered the threshold for investigation and referral to specialist care for cases of possible malignancy, including lung cancer (NG12) [8].

Imaging has become embedded into an increasing range of patient pathways, with the number of investigations performed in England doubling in 9 years [9]. Service challenges for radiology in the UK are threefold; sustained increases in activity [9, 10], a chronic shortage of consultant radiologists [11, 12] and unprecedented economic restrictions [13]. Recognising the need to improve patient outcomes for cancer, especially lung cancer which has shown minimal improvement in survival rates [2, 5], renewed focus is being given to rapid referral and diagnosis in cases of suspected cancer [6, 8, 14]. These initiatives will undoubtedly increase the volume of imaging investigations performed at a time when diagnostic capacity is failing to meet current demand [15].

A clinical report of imaging examinations is essential to guide diagnostic and treatment decisions. Time to a clinical report can be a serious factor in diagnostic delays [16–18] with recognition that small delays for lung cancer diagnosis may contribute to higher stage at diagnosis [19] and also a deterioration in performance status that may influence suitability for treatment. In the setting of the lung cancer pathway, delays are often multifactorial, but may be contributed to by the time taken to report a chest X-ray (CXR). This is because the very first step in the lung cancer pathway is often the identification and reporting of a lung mass on a CXR, which should then trigger a staging computed tomogram (CT). The use of appropriately trained radiographers to undertake clinical reporting is not new. Skeletal radiograph reporting, for example, has become widespread across the UK [12, 20], and in many departments provides a significant contribution to reporting capacity [21, 22]. More recently, reporting radiographers have been trained to report CXRs [23, 24] and this has been proposed as a method of minimising CXR reporting times in patients with suspected lung cancer [25]. There is some limited evidence to date that has evaluated CXR accuracy rates of trained reporting radiographers in comparison with radiologists. Reporting radiographers (*n* = 40) were found to have high sensitivity (95.4%; 95% CI 94.4–96.3%) and specificity (95.9%; 95% CI 94.9–96.7%) at an objective, structured examination of 100 CXRs at the completion of an accredited training programme [23].

Recent work found poor compliance with suggested optimal diagnostic investigations for lung cancer, with 23% of patients in England receiving investigation and results within the recommended timeframes with significant variation between regions [26]. This study aims to evaluate the impact of radiographer reporting on the timeliness, accuracy and quality of CXR reports, as well as the impact on the overall lung cancer pathway in comparison with radiologists. These parameters have not previously been studied in lung cancer patients. The current study could act as a pilot study for a larger, multisite evaluation if results are positive.

## Methods

The aim of the current study is to investigate the impact of radiographer immediate CXR reporting on the lung cancer pathway.

### Trial design

A two-way comparative study that will compare the time to diagnosis of lung cancer for patients. Internal comparison will be made between those who receive an immediate radiographer report of a GP CXR compared to standard radiographer GP CXR reporting (Fig. 1). The intervention group will receive an immediate CXR report and be offered a CT for CXRs suspicious for cancer. The control group will have the CXR reported no later than next working day in line with current protocols. Key protocol elements are summarised in the SPIRIT (Standard Protocol Items: Recommendations for Interventional trials) 2013 Checklist [27] (Additional File 1) and Figure (Fig. 2).

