### Randomisation

Intervention is at an institutional level; individual patients will not be randomised. Half-day sessions will be randomised to intervention or standard practice, using a randomisation list provided by the study statistician. This is in line with previous studies that have examined the timing or order of X-ray reading but where all examinations are requested as part of routine clinical care and receive reports from the same practitioners [30].

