### Outcome measures

The primary outcome is to test the impact of radiographer immediate reporting of GP CXRs, with immediate CT where appropriate, on time from performance of the CXR to treatment (with intermediate time points)/discharge for lung cancer.

Secondary outcome measures include:Measurement of the effect on the speed of the lung cancer pathway:
(i)6-and 12-month survival (lung cancer and all-cause)(ii)Number of emergency admissions for lung cancer(iii)Performance status at time of decision to treat(iv)Stage at diagnosis of lung cancer
Measurement of the effect of the pathway on efficiency including:
(i)The impact of immediate GP CXR reporting on the number of urgent respiratory cancer (2WW) referrals(ii)The accuracy and usefulness of radiographer CXR reporting in clinical practice(iii)The cost-effectiveness of radiographer reporting(iv)The influence of immediate GP CXR reporting, with immediate CT where appropriate, on the number of first 2WW appointments with all radiology results available
Measurement of the number of repeat CXRs performed in a timely fashion for suspected infectionThe effect of immediate reporting of GP CXRs on patient satisfaction

In addition to comparison as per randomisation within Homerton University Hospital, primary outcomes will be compared with a neighbouring hospital, Newham University Hospital.

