### Off-protocol radiographer reporting

Where the radiographer performing the CXR is concerned about the appearance of the X-ray or by the clinical condition of the patient, current practice at Homerton University Hospital is for the CXR to be reviewed by a reporting radiographer or a consultant radiologist prior to the patient leaving the department. This includes, for example, where the radiographer suspects a pneumothorax, tuberculosis or cancer. If a radiographer has concerns that the appearances of the CXR is abnormal and a significant pathology may be present, these patients will receive an immediate report, regardless of the reporting session allocation (immediate/standard) so as not to negatively impact on patient management. All such occurrences will be identified, included in the intention-to-treat principle, but we will also carry out sensitivity analysis excluding them. In view of randomisation, we expect the same rates of such cases in intervention and control sessions.

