#### Patient satisfaction

Patients referred for a CXR from GP will be identified by the radiology administration team, as is current practice. Eligible patients will have a Patient Satisfaction Survey posted to their home address, with a stamped self-addressed return envelope. No patient-identifiable data will be collected. Comparison will be made between patients who received an immediate and routine CXR report. The Patient Satisfaction Survey to be used has been included as an Appendix.

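### Patient satisfaction is to be compared by the report received rather than by the randomised session, which moves escalated control-session patients into the immediate group

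*Protocol article*

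**What the plan says.** All places are in the protocol article.

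- Randomisation: "Half-day sessions will be randomised to intervention or standard practice, using a randomisation list provided by the study statistician".
- Outcome measures, after the list of primary and secondary outcomes, which ends with patient satisfaction: "In addition to comparison as per randomisation within Homerton University Hospital, primary outcomes will be compared with a neighbouring hospital".
- Sample size: the figure of 26 cancers per group is given for the internal randomised comparison.
- Study setting, Control and Off-protocol radiographer reporting: a film that worries the performing radiographer is reported while the patient is still in the department, and this continues in control sessions. Off-protocol radiographer reporting also covers concern about the patient's clinical condition. On analysis it says "All such occurrences will be identified, included in the intention-to-treat principle", and it adds a sensitivity analysis without these films.
- Patient satisfaction: "Comparison will be made between patients who received an immediate and routine CXR report". The survey is posted to the patient's home, and "No patient-identifiable data will be collected".
- Trial design (and, in near-identical words, the abstract): "Internal comparison will be made between those who receive an immediate radiographer report of a GP CXR compared to standard radiographer GP CXR reporting". The sentences that follow describe what the intervention and control groups will get.

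**The concern.** A session-randomised comparison and a comparison by report received coincide only if every patient gets the report timing of the session. Here the protocol expects departures, and all that it describes run one way: some control-session patients get an immediate report. They are selected on an abnormal-looking film or on being unwell.

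If satisfaction is grouped by report received, these patients leave the control group and join the immediate group. Their answers may well differ from those of other patients, because some will have been told on the spot that something serious may be present. The direction is not obvious. Survey question 7, on feelings about further tests, offers fear, anger and upset, but also being pleased that something was happening. Either way, the satisfaction comparison would no longer have the protection of randomisation.

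**Working it through.** **Reading the sections together**

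1. Primary outcome. Randomisation is by session, the Outcome measures section compares as randomised, and the Sample size section sizes the randomised comparison. Off-protocol radiographer reporting deals with exactly the crossover films and puts them under intention to treat. The grouping is settled.
2. The stated sample size is consistent with this and is not affected: 2 × (1.960 + 0.842)² × 14² / 11² = 25.4, so 26 per group by the normal approximation, as stated.
3. Satisfaction. The only sentence specific to this outcome groups patients by the report they received. The off-protocol section does not name satisfaction.
4. The survey form. Answers are anonymous and no identifying data are collected. None of the printed questions records the session or its allocation. Survey question 4 asks only when the patient was told that results would be available. An escalated control-session patient could truthfully choose an immediate option, so this item reflects the report received and not the allocation.

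**What as-received grouping does to the groups**

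Assumptions: n survey patients allocated to each arm; the same fraction f in each arm would worry the performing radiographer (the protocol expects equal rates); all intervention-session films are reported immediately; return rates are equal.

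- Immediate group by receipt: n + fn patients, of whom fn + fn = 2fn are of the worrying kind. Their share is 2f/(1+f).
- Routine group by receipt: n(1−f) patients, none of them of the worrying kind.
- By randomised session: share f in both groups.

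Suppose immediate reporting has no effect on satisfaction, and a given answer is chosen by a proportion p₁ of the worrying kind and p₀ of the others. Then:

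- as received: difference = (p₁ − p₀) × 2f/(1+f);
- as randomised: difference = 0.

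Illustrative values of the multiplier, with f assumed:

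- f = 0.1: 0.2/1.1 = 0.18
- f = 0.2: 0.4/1.2 = 0.33
- f = 0.3: 0.6/1.3 = 0.46

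For small f the multiplier is close to 2f. The documents give no escalation rate among all GP chest X-ray patients and no value for p₁ − p₀. These lines therefore show the mechanism and do not estimate the bias.

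**What as-randomised grouping costs**

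Escalated control-session patients get an immediate report in either arm. If immediate reporting changes the others' answers by δ, the contrast by session is (1−f)δ: 0.9δ at f = 0.1, 0.8δ at f = 0.2 and 0.7δ at f = 0.3. This is dilution and not selection bias.

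**The case against.** The strongest reply is that the satisfaction sentence is shorthand. The article elsewhere uses immediate and standard as labels for the allocation: the off-protocol section does so in brackets, and the section on repeat X-rays for infection speaks of an immediate reporting arm and a standard care arm. The statement "In addition to comparison as per randomisation within Homerton University Hospital" follows a list that includes satisfaction, and the intention-to-treat sentence could be read as covering every outcome. A condensed article may also leave the satisfaction analysis set to an analysis plan that is not shown.

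Much of this stands. It is decisive for the primary outcome, and it shows that the Trial design and abstract wording is a loose summary and not a rule on analysis sets. The next sentence in Trial design, "The intervention group will receive an immediate CXR report and be offered a CT for CXRs suspicious for cancer", plainly describes an arm.

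It is weaker for satisfaction. There the one outcome-specific statement says received, and the printed form offers an item that matches that reading and none that matches allocation. An analysis plan could restate the grouping, but it could not recover allocation from anonymous returns that were never marked. The article does not describe such a mark. One may exist outside it, in which case only the sentence needs changing.

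**Conclusion.** The point holds for patient satisfaction, a secondary outcome. Followed as written, the Patient satisfaction section moves a selected set of control-session patients into the immediate group. The resulting bias is (p₁ − p₀) × 2f/(1+f) for any given answer under no true effect. Its direction and size cannot be computed, because the documents give neither f nor p₁ − p₀. It would be small if escalation is rare among GP films.

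A reader might infer from the Trial design wording that the primary comparison of times is also as received, and that it could show a false gain. For example, if 20% of control cancers were escalated and were inherently 10 days faster, the spurious difference would be 10 × 0.4/1.2 = 3.3 days, with an inflated type I error. The documents do not support that inference. The Randomisation, Outcome measures, Off-protocol radiographer reporting and Sample size sections together fix an as-randomised analysis, with a sensitivity analysis excluding the escalated films. Such figures would size an analysis that is not planned, and both of their inputs are assumed.

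**What to change.** - In the Patient satisfaction section, state that patients are compared by the allocation of the half-day session in which their chest X-ray was taken, whatever report timing they received.
- Print a non-identifying session-allocation code on each survey before it is posted. Allocation is known from the date and time of the film, and a two-value code adds no identifying data.
- Align the Trial design section and the abstract with the same wording. No other rule or figure changes, and the handling of worrying films in control sessions is untouched.

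The cost is slightly more than wording: the administration team must mark the forms before they go out, since this cannot be done once anonymous returns arrive. The as-randomised satisfaction contrast will be somewhat diluted by escalated control-session patients, by the factor 1−f. The sample size is unaffected.

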**Fig. 1 Fig1:**
[figure not shown]
Intervention and standard patient pathway at Homerton University Hospital and Newham General Hospital (external comparator). *GP* general practitioner, *CXR* chest X-ray, *CT* computed tomography, *RR* reporting radiographer, *CR* consultant radiologist, *Other Resp* other respiratory disease, *sus CA* suspicious for cancer, *2WW* urgent respiratory referral for suspected cancer, *Routine Resp* routine referral to respirator medicine

**Fig. 2 Fig2:**
[figure not shown]
Schedule of enrolment, interventions and assessments. C*XR* chest X-ray, *CT* computed tomography scan, *when required

The diagnostic aspect of the lung cancer pathway at Homerton University Hospital is relatively streamlined. To enable comparison with radiology service delivery at other institutions’ time to diagnosis (immediate and standard CXR reporting) will be compared with Newham University Hospital (Fig. 2). This adjacent hospital has comparable patient demographics, a similar number of lung cancer patients per year and is of comparable size. Newham does not currently have CXR-reporting radiographers and does not offer a straight-to-CT service for CXRs suspicious for lung cancer.

### Study setting

Research Ethics Committee and Health Research Authority approval was granted on 6 June 2017 (REC 17/LO/0870; HRA 221968). This study will not directly recruit patients; it is an evaluation of health service delivery and, as such, no patient consent is required. Intervention is at an institutional level and institutional approval has been gained. No additional or different tests will be performed, and all the reporting practitioners (reporting radiographers and consultant radiologists) currently report CXRs in clinical practice. The comparative aspect of the study is the timing, accuracy and usefulness of the CXR report; immediate compared to standard care. Patient-identifiable data will not be available outside of the direct clinical care team, only anonymised data will be used. Patients will be assigned a unique study identifier at time of CXR by the clinical care team. Block randomisation, institutional rather than patient enrolment and the use of de-identified data is in line with previous research that has examined the order of interpretation between readers [28]. The intervention is considered to be an alternative, non-inferior form of standard practice since radiographer reporting of CXRs has already been implemented in some NHS trusts in the UK. Radiographer reporting, including CXRs, has been shown to create additional diagnostic capacity at centres that have embedded this into the imaging department [21, 22, 29]. However, the published evidence on radiographer reporting of CXRs is limited. Furthermore, robust methods of evaluating diagnostic reports (including actionability and usefulness) of radiographers and radiologists using independent experts has not previously been attempted.

Clinical assessment will be made by a general practitioner and a referral made to Homerton University Hospital for a CXR examination following standard and established referral procedures. The referral for CXR will be checked by the performing radiographer or supervised assistant practitioner to ensure that the referral meets Ionising Radiation (Medical Exposure) Regulations (IRMER) (2000) requirements and adheres to departmental protocols for a justified referral. Chest X-rays will be obtained using digital radiography equipment, and radiation doses will be as low as possible while maintaining good image quality. Existing departmental imaging protocols will be followed. The standard X-ray projection for a chest examination is a single posterior-anterior (PA) X-ray. The radiographer or assistant practitioner will check all images for diagnostic quality and record the radiation dose on the Radiology Information System (RIS) in line with departmental standard operating procedures. If the radiographer or assistant practitioner performing the CXR identifies a potentially significant abnormality; for example, lung cancer or pneumothorax, this will be triaged for an immediate report according to current protocol.

Inclusion and exclusion criteria are presented in Table 1.

**Table 1 Tab1:** Inclusion and exclusion criteria

	Criteria
Inclusion	• Referred for a chest X-ray from general practice
	• Aged over 16 years
Exclusion	• Active diagnosis of lung cancer

### Randomisation

Intervention is at an institutional level; individual patients will not be randomised. Half-day sessions will be randomised to intervention or standard practice, using a randomisation list provided by the study statistician. This is in line with previous studies that have examined the timing or order of X-ray reading but where all examinations are requested as part of routine clinical care and receive reports from the same practitioners [30].

### Intervention

The intervention reporting strategy is modelled on the National Optimal lung cancer pathway developed in 2016 [31]. The intervention strategy aims to streamline the patient journey through the lung cancer pathway by providing prompt interpretation of CXRs referred by general practice (GP) and offering immediate CT when appropriate.

Chest X-rays included in the intervention arm will be reported at the time of image acquisition while the patient is still in the radiology department. Patients who have a CXR suspicious for cancer will be offered an immediate CT of the chest and upper abdomen.

